## Abstract

**Background:**

Late effects can occur years to decades after cancer therapy, resulting in morbidity and reduced health-related quality of life. Clinical long-term follow-up (LTFU) enables timely diagnosis and treatment of these sequelae. So far, only a minority of childhood cancer survivors (CCS) in Germany regularly visit LTFU care facilities.

The LE-Na study aims to: 1. implement and/or improve LTFU care structures for adult CCS in Germany, 2. inform former patients about late effects and LTFU care centers, 3. create a basis for future research by building up a central database, consent management and infrastructure, 4. establish a clinical LTFU cohort of adult CCS in Germany, 5. evaluate the implementation of the LFTU care, 6. enable the expansion of LTFU care structures nationwide, 7. integrate the developed LTFU care structures into the standard health care system.

**Methods:**

Within five years, approximately 5000 CCS will be invited to visit one of the 10 LTFU centers in Germany. Study participants are either contacted by the German Childhood Cancer Registry (GCCR), transitioned from the local pediatric oncology care unit, or recruited via media. They are assigned to one of three different risk groups based on an evidence-based risk stratification and receive standardized multidisciplinary follow-up care.

Primary outcomes are satisfaction with the LTFU care offer as well as degree of health-related self-efficacy expectation. They will be assessed at two time points. A scientific evaluation of the implemented LTFU care will be enabled by a waitlist control group. The harmonized outcome data are documented in a standardized database.

**Discussion:**

By addressing CCS in Germany who have not received standardized LTFU care yet, the LE-Na study expects to improve nationwide LTFU care and therewith patient’s satisfaction with the LTFU care offer as well as their health-related self-efficacy expectation.

## Introduction

During the last decades, cancer treatment improved continuously resulting in a growing community of childhood cancer survivors (CCS) worldwide [1]. As these survivors often face chronic health conditions, manifesting later in life as a consequence of the former cancer treatment, risk-adapted long-term follow-up (LTFU) is recommended to facilitate timely diagnosis and treatment of possible late effects [2]. However, only a few specialized survivorship care units have been established in Germany to date. Additionally, as most studies focusing on late effects of cancer treatment have been conducted during the last two decades, many CCS that were treated prior to 2000 have not been informed about their individual risk for late-effects nor have they been invited to regular LTFU [3, 4].

Consequently, the multi-centric, prospective LE-Na study has been developed in order to implement and evaluate multidisciplinary, standardized, guideline-based LTFU care for adult survivors of childhood cancer in Germany and thus improve survivorship care nationwide.

Following on from previous pilot studies, LE-Na pursues seven objectives [4, 5]. First, to expand multidisciplinary LTFU structures to improve detection and treatment of late effects as well as psychosocial challenges and mental health impairments in CCS. Second, to provide appropriate information about late effects and recommendations for LTFU care for CCS who were treated in the 1980s and 1990s as they may not have been informed about late effects yet. Third, to create a platform for future research by building up a central database, consent management and infrastructure. Fourth, to establish a clinical LTFU cohort of German CCS in order to prospectively gain knowledge on late effects. Fifth, to evaluate the implementation of the LTFU care. Sixth, to enable the expansion of LTFU structures nationwide by offering harmonized and evaluated procedures as well as documents to clinics that do not have a survivorship care unit yet. And seventh, allowing the integration of LTFU care structures as developed and evaluated in this project into the standard health care system.

## Methods

### Study design

LE-Na is a prospective, multi-center study which will be conducted in 10 LTFU clinics in Germany. Further clinics will be invited to participate during the study period as soon as they have set up a multidisciplinary LTFU team and follow the evidence-based risk stratification used in LE-Na [3, 6] (see Fig. 1).

**Fig. 1 Fig1:**
[figure not shown]
German LTFU clinics currently participating or in preparation to participate in the LE-Na trial. Lübeck – University Hospital of Schleswig–Holstein, Campus Lübeck. Hamburg—University Hospital Hamburg-Eppendorf. Berlin –University Hospital Charité Berlin. Hannover – University Hospital Hannover. Dresden—University Hospital Carl Gustav Carus, Dresden. Bonn—University Hospital Bonn. Frankfurt—University Hospital Frankfurt am Main. Mainz—University Hospital of the Johannes Gutenberg-University Mainz. Erlangen—University Hospital Erlangen. Tübingen—University Hospital Tübingen. Augsburg – University Hospital Augsburg. Munich—University Hospital Rechts der Isar, Munich. Freiburg –University Hospital Freiburg

The LE-Na trial was preceded by several feasibility studies and the components were constantly reevaluated [4, 5]. An external advisory board as well as a representative of German health insurance companies participate in study meetings and advise the study consortium. However, they do not have access to study data. Survivors representatives as well as health economic specialists have been included in study preparation but, due to organizational issues, do not participate in study meetings.

During the study period of five years (January 1st 2023 to December 31st 2027), primary outcomes will be assessed in a pre-post-comparison (outcomes and measurements see Table 1). Therefore, after giving consent, study participants will be asked to complete a set of questionnaires at the initial consultation at the LTFU clinic as well as after three years (phase 1). The first assessment always takes place at the clinic and is tablet-based; the second assessment after three years can either take place at the clinic during regular LTFU (participants from risk group 2 and 3, see also “standardized LTFU care and risk stratification”) or web-based/ on paper if the participant is not regularly attending the clinic in this year. The results of the survey, all examination results and medical history will be documented in a pseudonymous form in a clinical trial management system (CTMS) in order to enable a central and coherent recording of late effects [5].

**Table 1 Tab1:** Primary and secondary study outcomes

Category	Instrument/measurement
**Primary outcomes**	
Satisfaction with the LTFU care offer	Patient Satisfaction Questionnaire-Short Form, PSQ-18^a^
Degree of health-related self-efficacy expectation	General Self-Efficacy-Scale (GSE)^a^
	Healthcare Self-Efficacy-Scale – (HCSE)
**Secondary outcomes**	
Implementation of guideline recommendations in specialized LTFU care centers	Operationalized as use of risk stratification and guideline recommendations by the study centers (annual survey)
Health related quality of life	EORTC QLQ C30
Incidence and prevalence of late effects	

^a^Instructions of the PSQ-18 and GSE have been slightly adapted to set the questionnaire into the context of LTFU after childhood cancer

Additionally, during study year 3 and 4 (phase 2), the implementation of LTFU care will be tested randomized using a waiting list control group, again, regarding the primary endpoints. This intervention was developed together with health economists in order to provide evidence for the benefit of standardized LTFU care that can be used to obtain full cost coverage by the health insurance companies. All potential study participants in this phase are contacted by the GCCR and are asked to participate in this randomized trial. Randomization is carried out by the GCCR that defines a group of potential participants that is stratified according to gender, cancer diagnosis, time since end of therapy and residency. Participants of the intervention group in phase 2 receive an invitation to visit the LTFU clinic within the following three months. They complete the questionnaires web-based before their first visit as well as after 12 months. Participants of the waiting control group receive an invitation to complete the questionnaires web-based initially and a second time after 12 months. After filling out the questionnaire at these two time points, the waiting control group visits the LTFU clinic (one year later than the intervention group) and receives the same standardized LTFU care.

### Study population

Currently, about 1000 patients visit one of the LTFU care centers in Germany per year, which corresponds to about 3% of adult CCS in Germany. The LE-Na study aims to bring additional 5000 survivors into regular LTFU care through three different recruitment strategies:Regular transition from the pediatric care unitInvitation to participate in the LE-Na study sent out to 5000 CCS by the German Childhood Cancer Registry (GCCR) [7], fulfilling the following criteriainitially treated for childhood cancer between 1980 and 1999Living within a radius of 50–100 km from one of the study centersmedia, e.g. flyer, survivor meetings, project homepage, social media

Inclusion criteria for the LE-Na study are:
18 years or older at the time of study inclusioncancer diagnosis and therapy in childhood or adolescence (before 18.^th^ birthday)completed regular oncological follow-up care (at least 5 years after end of treatment of the primary oncological disease)in case of relapses or secondary neoplasia: at least 6 months after completion of radiotherapy/chemotherapy, at least 12 months after completion of stem cell transplantationgood understanding of the German language

Exclusion criteria of the LE-Na study are:people not capable of giving consentalready received interdisciplinary LTFU carecurrent oncological therapy

### Ethics approval and consent to participate

This study was approved by the ethics committee of the University of Lübeck (registration number 2022–647). Given informed consent is required to participate in the study.

Potential participants in phase 1 will be informed about the study prior to the initial consultation and, if interested, asked to give their written informed consent by the physician in charge as soon as they visit the LTFU clinic. Participants document on the informed consent form whether they want to be contacted via e-mail or mail to fill out the second questionnaire after three years if they do not attend the clinic at this time during their regular LTFU.

Potential participants of the waiting list control design (phase 2), will be invited to take part in the study via mail by the GCCR. The invitation contains information about the random allocation to the intervention or the waiting control group and explains that the randomisation result will be communicated at a later date. If CCS are interested to participate, they contact a LTFU clinic of their choice by telephone. Each LTFU center has an ID list of all CCS contacted by the GCCR along with the randomisation results. The respective LTFU center coordinator asks the CCS if they confirm study participation in the randomization trial. If the CCS agrees, the LTFU center coordinator records the CCS's contact data and informs the CCS afterwards by email about the randomisation result and a proposed date for the first LTFU appointment. The participant also receives a link to a portal (e.g. SoSci Survey) to fill in the questionnaires web-based before the first consultation in the clinic. Prior to answering study items, participants have to read the study information and give their consent by ticking the regarding consent-statement. They also have to fill in their study ID, provided in the invitation letter sent by the GCCR, to identify themselfes. The follow-up survey after one year will also be sent to the participants via the respective centres (as in phase 1). CCS who are interested in LTFU care but refuse to participate in the randomisation trial before they were informed about the randomization result are asked to participate in the pre-post-comparison (phase 1).

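### In phase 2 the enrolling centre holds the randomisation results before it asks survivors to confirm participation, so allocation is not concealed from the recruiter; consent and baseline also follow disclosure of the arm

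*Protocol article*

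**What the plan says.** The phase 2 procedure is described in two places in the protocol article.

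- **Study design (the phase 2 paragraph after Table 1).** Allocation is done centrally, within a predefined group: "Randomization is carried out by the GCCR that defines a group of potential participants that is stratified according to gender, cancer diagnosis". The group consists of potential participants, so the arm exists before the survivor has responded. The control arm visits the clinic one year later than the intervention arm. Both arms complete the questionnaires online at the start and after 12 months.
- **Ethics approval and consent to participate.** The invitation letter mentions random allocation and "explains that the randomisation result will be communicated at a later date". An interested survivor telephones a centre. On what the centre knows by then, the text says: "Each LTFU center has an ID list of all CCS contacted by the GCCR along with the randomisation results". The next step is: "The respective LTFU center coordinator asks the CCS if they confirm study participation in the randomization trial". If the survivor agrees, the coordinator records the contact data and "informs the CCS afterwards by email about the randomisation result and a proposed date for the first LTFU appointment". The survivor also receives a portal link, where the consent statement is ticked before the study items are answered.

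The same section directs to phase 1 those survivors who want care but "refuse to participate in the randomisation trial before they were informed about the randomization result". Phase 1 starts with questionnaires at the initial clinic consultation and has no waiting arm.

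**The concern.** Allocation concealment requires that the person who enrols a participant cannot foresee the assignment. When randomisation precedes agreement, leaving out those who do not confirm is harmless only if confirmation is unrelated to the arm. Here the enrolling centre has the arm for every ID in advance, and the design offers an alternative route that avoids the one-year wait. A coordinator who knows that a caller with complaints is a control has an understandable reason to mention that route more readily, without any bad faith.

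There is a second exposure in the same section. Recorded consent and the baseline questionnaire appear to come after the survivor has learned the arm. A survivor told to wait a year may not open the portal, or may answer the baseline satisfaction and self-efficacy items differently.

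Both primary outcomes are self-reported and the arms cannot be blinded, so concealment at enrolment is one of the few protections available. The Study design section says the randomised phase is meant to provide evidence for full cost coverage by health insurers. Adjusting for primary disease, sex and time since treatment, as planned under Statistical analysis, would not remove selection on symptoms or motivation.

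**Working it through.** **1. Sequence of events, from the two sections**

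| Step | Who acts | Is the arm known to the centre? | Is the arm known to the survivor? |
|---|---|---|---|
| Randomisation of potential participants | GCCR | – | no |
| ID list with results held at centre | centre | yes | no |
| Invitation letter, then telephone call | GCCR, survivor | yes | no |
| Request to confirm; refusers asked to join phase 1 | centre coordinator | yes | no |
| Email with result, appointment date and portal link | centre coordinator | yes | yes |
| Consent tick and baseline questionnaire in portal | survivor | yes | yes |

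The survivor is masked up to confirmation. No step masks the centre: the article describes no access restriction, no release of single results and no independent enroller. The last row shows the second exposure.

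**2. The plan's sample size**

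Statistical analysis gives delta = 0.25, power 80%, and 310 per group for two endpoints or 255 per group for one. The phase 2 alpha is not stated. With SD = 1 and n per group = 2 × ((z for alpha + z for power)/delta)²:

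- two-sided 2.5% (5% shared by two endpoints, assumed): 2 × ((2.241 + 0.842)/0.25)² ≈ 304, or 305 rounded up; the plan has 310
- two-sided 5% (one endpoint): 2 × ((1.960 + 0.842)/0.25)² ≈ 251, or 252 rounded up; the plan has 255

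Both reproduce within 3%, which supports 2.5% as the working alpha below. The sample size is not in dispute.

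**3. Illustration of selective loss from the control arm**

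The diversion figures are assumptions; the document gives none. Let a share f of control-allocated callers be diverted to phase 1, scoring d SD worse than the control mean. The mean of the remaining controls then rises by f × d/(1 − f). With 310 analysed per arm, SE = √(2/310) = 0.0803. Power to show benefit is Φ((0.25 − shift)/SE − 2.241).

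- No diversion: 0.25/0.0803 = 3.112; power Φ(0.871) ≈ 81%.
- f = 5%, d = 0.2: shift 0.05 × 0.2/0.95 ≈ 0.01 SD, 4% of delta; power ≈ 77%.
- f = 10%, d = 0.5: shift 0.10 × 0.5/0.90 = 0.056 SD, 22% of delta; power Φ(0.194/0.0803 − 2.241) = Φ(0.179) ≈ 57%.
- f = 20%, d = 0.5: shift 0.20 × 0.5/0.80 = 0.125 SD, 50% of delta; power ≈ 25%.

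If the diverted controls are not replaced (310 against 279 when f = 10%), power in the third case is about 55%.

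**4. Direction**

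In these cases the worse-scoring controls leave, so the remaining controls look better and the bias runs against the intervention. With no true effect, f = 10% and d = 0.5, shift/SE = 0.69. The chance of a false finding of harm is P(Z > 2.241 − 0.69) ≈ 6.1%. The chance of a false finding of benefit falls from 1.25% to about 0.17%. If better-scoring controls were lost instead, the two figures would swap and the error would favour the intervention.

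**The case against.** The article does include safeguards. The letter withholds the result, and the phase 1 route is worded for people who decline before learning it. This blocks self-selection by survivors up to confirmation, and it stands. It does not address what the recruiter knows.

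The text places the list at the centre, not expressly in the coordinator's hands. That is correct. But the coordinator belongs to the centre and sends out the result, and no barrier is described. Nor does the text promise immediate care in phase 1; it gives no appointment interval, only no planned one-year wait. Steering is a possibility left open, not something the plan intends.

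Two stronger readings are tempting but not supported:

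- **That the two sections contradict each other on when the arm is disclosed.** Study design says: "Participants of the intervention group in phase 2 receive an invitation to visit the LTFU clinic within the following three months". A reader might take this as an arm-specific recruitment letter. But it speaks of participants, after saying that all potential participants are contacted and asked to join, and it fits the email sent after confirmation. The sections are compatible.
- **That the flaw inflates false claims of benefit.** At f = 10% and d = 0.5 the total type I error is about 6.2%, but nearly all of it is false harm. A false claim of benefit becomes less likely, and the cost is lost power.

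**Conclusion.** The concern holds as a failure of allocation concealment built into a stated procedure: the recruiting centre has the results before it asks for confirmation. In the order given, recorded consent and baseline also follow disclosure to the survivor. This does not rest on any figure, and it is not something the article leaves to a fuller document.

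The size and sign of the bias cannot be derived from the document. Under the assumed inputs (310 per arm, SD 1, two-sided alpha 2.5%) the shift ranges from about 0.01 SD, which is negligible, to 0.056 SD with power down from about 81% to about 57%, and further if diversion is heavier. Selection the other way would favour the intervention. The planned numbers of 310 and 255 per group are unaffected.

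**What to change.** - Remove the randomisation results from the centre ID lists. The GCCR, or central data management, keeps them.
- Release the arm for a single ID only after the centre has logged the confirmation **and** the participant has completed the online consent and the baseline questionnaire. Release after telephone confirmation alone would still allow arm-dependent loss before consent and arm-dependent baseline answers.
- Report confirmation, refusal and phase 1 diversion rates by allocated arm. This is possible because every contacted ID is already randomised, and it also gives a check on anyone enrolled under the present procedure.

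The cost is one central look-up per participant, a short change of procedure at the centres, and a small delay in communicating the appointment. The sample size does not change.

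### In phase 2, participants learn their arm before they consent and complete the baseline questionnaire, so baseline scores and entry into the sample can depend on allocation

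*Protocol article*

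**What the plan says.** The phase 2 procedure is set out in the protocol article under Study design (the text after Table 1) and under Ethics approval and consent to participate. In order, the steps are:

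1. The registry randomises before anyone has agreed to take part: "Randomization is carried out by the GCCR that defines a group of potential participants that is stratified according to gender, cancer diagnosis".
2. The invitation letter describes the random allocation but withholds the result; it "explains that the randomisation result will be communicated at a later date".
3. The centres already know the result: "Each LTFU center has an ID list of all CCS contacted by the GCCR along with the randomisation results".
4. The survivor telephones a centre. "The respective LTFU center coordinator asks the CCS if they confirm study participation in the randomization trial".
5. If the survivor agrees, the coordinator "informs the CCS afterwards by email about the randomisation result and a proposed date for the first LTFU appointment".
6. "The participant also receives a link to a portal (e.g. SoSci Survey) to fill in the questionnaires web-based before the first consultation in the clinic".
7. In the portal, "Prior to answering study items, participants have to read the study information and give their consent by ticking the regarding consent-statement".

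Study design says of the intervention arm: "They complete the questionnaires web-based before their first visit as well as after 12 months". Controls answer at the start and again at 12 months. Neither statement places the first questionnaire before disclosure of the arm.

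The ethics section makes informed consent a condition of participation. It offers phase 1 to people who decline the randomised comparison before hearing their result. It gives no rule for people who agree by telephone, hear their result and then never tick consent.

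**The concern.** Both primary outcomes are self-reports: satisfaction with the care offer (PSQ-18) and self-efficacy (GSE, HCSE). They are first measured after one arm has been offered an early appointment and the other has been told to wait about a year. Satisfaction with an offer could plausibly respond to that news, so the first questionnaire is not a measurement free of allocation.

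Consent also follows the news. Someone disappointed by the result can stop without providing any data, and such losses can differ between arms.

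The coordinator who asks for confirmation can see the allocation, so it is not concealed from the person who enrols.

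Phase 2 is intended to supply evidence for full cost coverage by the health insurers. An error in either direction would therefore matter.

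**Working it through.** **Planned sample size.** The Statistical analysis section gives delta = 0.25, power 80% and 310 per arm for two primary endpoints, or 255 per arm for one. It does not state the phase 2 alpha; 0.05/2 = 0.025 two-sided is assumed here for two endpoints.

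- Formula: n per arm = 2 × ((z for alpha + z for power)/delta)².
- Two endpoints: 2 × ((2.241 + 0.842)/0.25)² ≈ 304.2, so 305, against 310 stated.
- One endpoint at two-sided 0.05: 2 × ((1.960 + 0.842)/0.25)² ≈ 251.2, so 252, against 255 stated.

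Both agree within 3%. No figure in the plan is wrong; the point concerns the order of steps.

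**Illustration A: disclosure shifts one arm's baseline by 0.10 SD.** Assumed: no true effect, baseline-to-12-month correlation r = 0.5, unit SD, 310 per arm, critical value 2.241. The rejection probability is P(|Z + m| > 2.241), with m = bias/(SD × √(2/310)) and √(2/310) = 0.0803.

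| Analysis | Bias | SD | m | Rejection under the null |
|---|---|---|---|---|
| 12-month score only | 0 | 1 | 0 | 2.5% |
| Baseline-adjusted | r × 0.10 = 0.05 | √(1 − r²) = 0.866 | 0.72 | about 6.5% |
| Change score | 0.10 | √(2(1 − r)) = 1 | 1.245 | about 16% |

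As shares of delta, the two biases are 0.05/0.25 = 20% and 0.10/0.25 = 40%.

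Over assumed shifts of 0.05 to 0.15 SD, rejection under the null ranges as follows:

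| Analysis | r = 0.5 | r = 0.7 |
|---|---|---|
| Change score | 5.5% to 35% | 7.6% to 57% |
| Baseline-adjusted | 3.5% to 12% | 5.4% to 34% |

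**Illustration B: selective loss after disclosure.** Assumed: 10% of controls leave, and their outcome mean is 0.5 SD worse than that of those who stay. The remaining control mean moves by 0.10 × 0.5 = 0.05 SD (20% of delta). With 310 against 279, rejection under the null is about 5.3%. A 20% loss gives 0.10 SD and 14%; a 30% loss gives 0.15 SD and 29%. If the leavers do not differ at all, power still falls from 80.8% to 78.5%, 75.6% and 72.0%. This route operates whichever score is analysed.

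**Direction.** If disclosure lowers the control baseline, controls appear to improve more. If worse-scoring controls leave, the control mean rises. Both work against follow-up care. For the change score with 0.10 SD bias, almost all of the 16% consists of rejections in favour of waiting; the share in favour of follow-up care is about 0.02%, against a nominal 1.25%. With a true effect of 0.25, that bias leaves an apparent effect of 0.15. Power is then P(Z > 2.241 − 0.15/0.0803) = P(Z > 0.374), about 35% instead of about 81%.

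**The case against.** Four counter-arguments carry weight.

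- **Agreement precedes disclosure.** Invitees know about the random allocation and confirm participation before they hear the result. Later selection is confined to people who accepted a possible wait. This stands as a limit on the bias, but the telephone agreement is not the consent that the study requires, so the route stays open.
- **Baseline may not enter the analysis.** The Statistical analysis section calls phase 2 a parallel group comparison and names primary disease, sex and time since treatment as covariables. Baseline score is not among them, and details are left to a statistical analysis plan that is not shown. A comparison of 12-month scores alone would be free of baseline bias. This stands, but it does not remove selection.
- **The losses are partly recoverable.** Centres record contact data before disclosure, so non-starters can be reminded. The registry holds the stratification variables for everyone randomised, so losses can be compared by arm and weighted. This stands too, although weighting cannot remove selection on unmeasured factors.
- **The sizes are assumed.** The document gives no estimate of a disclosure effect or of loss after disclosure.

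A reader might infer that the baseline and sample certainly are distorted, or that the trial is likely to claim a benefit that does not exist. The document supports neither. It opens a route to bias without showing that bias occurs, and in the two scenarios whose direction is worked through, the bias runs against follow-up care. The opposite direction is possible but equally undemonstrated.

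**Conclusion.** The point holds as a weakness in the order of steps. As written, the required consent and the self-reported baseline both follow disclosure of the arm, and the coordinator seeking confirmation knows the allocation. Baseline scores and entry into the sample can therefore depend on allocation.

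Selection is the more robust half, because it does not depend on the analysis model. The baseline half applies only if the analysis uses change scores or adjusts for baseline.

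The magnitude is unknown. The percentages above rest on an assumed alpha of 2.5%, assumed correlations and assumed shifts or losses; they show that small shifts are not negligible beside a planning effect of 0.25. In the directions illustrated, the practical harm is an underestimated benefit and lost power.

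**What to change.** Change the order in the phase 2 procedure:

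- After telephone confirmation, send only the consent and baseline link.
- Release the randomisation result and the appointment date to the participant once consent and baseline have been submitted. Preferably withhold the result from the coordinator until then as well; a second email alone would leave the coordinator's prior knowledge untouched.
- Analyse everyone who submitted the baseline, in the arm to which they were randomised.
- Report by arm the numbers confirmed by telephone, consented and with a baseline questionnaire.

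The cost is one extra email, a wording change and reminders to non-starters. Scheduling would wait for the survey, which causes a short delay that has to be fitted into the three-month invitation window of the intervention arm. Withholding the list from coordinators also requires a release step between registry and centre. No additional patients or visits are needed.
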